
**Figure 1 Fig1:**
[figure not shown]
**Flow chart of the current trial.** ETV, entecavir; HBV, hepatitis B virus; HBsAg, hepatitis B surface antigen; HCC, hepatocellular carcinoma; RGT, tablet of compound *biejia ruangan*; TCM, traditional Chinese medicine.

This study is being conducted in accordance with the ethical principles of the Declaration of Helsinki and is consistent with GCP guidelines and applicable local regulatory requirements. Written informed consent is obtained from all randomly assigned patients.

The primary end points in this study are the occurrence of HCC or liver-related mortality. HCC is diagnosed either histologically or clinically based on guidelines proposed by the Chinese Liver Cancer Study Group [19]. According to these criteria, patients are considered positive for HCC if they have one or more risk factors (hepatitis B or C virus infection, or cirrhosis) and one of the following: (1) serum α-fetoprotein (AFP) >400 ng/mL and a positive finding on at least one of three typical imaging studies [dynamic computed tomography (CT), dynamic magnetic resonance imaging (MRI) or hepatic angiography] or (2) serum AFP <400 ng/mL and positive findings on at least two of the three imaging studies. A positive finding for typical HCC on dynamic CT or MRI is defined as increased arterial enhancement followed by decreased enhancement compared with the liver (washout) in the portal or equilibrium phase. Liver-related mortality is defined as death caused by hepatic decompensation (regardless of etiology) or HCC.

Secondary end points are disease progression and overall survival rate. Disease progression is defined as either histological progression reflected by an increase in METAVIR score of at least 1 point or clinical progression reflected by the occurrence of decompensated cirrhosis. Decompensated cirrhosis is defined by the development of complications of portal hypertension (ascites, variceal hemorrhage, hepatic encephalopathy or spontaneous bacterial peritonitis) and/or liver insufficiency (jaundice). Following previous studies [20, 21], liver biopsies are collected at three defined time points: before the start of randomization (unless a biopsy has been performed within 3 months of randomization), at week 72 of the double-blind treatment and at month 24 of the open-label treatment during follow-up. Every patient with liver biopsy of at least six portal tracts is included in the study. To ensure the quality of liver tissue specimens for pathological assessment, liver biopsies in all centers is performed using unified 16G liver biopsy needles and a modified Jamshidi Menghini needle (Allegiance Corporation, McGaw Park, IL, USA), and the tissue is fixed in formalin and embedded in paraffin. Two independent third-party pathologists who are unaware of the patients’ treatment assignment, biopsy sequence and clinical outcome will examine all biopsy slides.

Hepatic fibrosis is assessed by the METAVIR system for fibrosis stage and necroinflammatory activity as a hard index [22, 23]. The fibrosis stages are: no fibrosis (F0), mild fibrosis (F1), moderate fibrosis (F2), severe fibrosis (F3) and cirrhosis (F4). Necroinflammatory activity is: no activity (A0) mild activity (A1), moderate activity (A2) and severe activity (A3). Serum fibrosis biomarkers including Fibrotest, aspartate aminotransferase to the platelet ratio index (APRI), liver stiffness spleen diameter to platelet ratio score (LSPS), and FibroMeters and FibroScan are used to assess hepatic fibrosis as a surrogate index [24, 25]. Hard and surrogates indexes are evaluated at all three time points (baseline, week 72 and week 96 after the open label) for each patient. Changes in liver fibrosis from baseline to weeks 72 and weeks 96 after the open label are analyzed on available pooled data using the METAVIR scoring system and the surrogate index.

The contraindications of liver biopsy include coagulopathy, uncooperative patients, impaired mental status, infection of the hepatic bed and extrahepatic biliary obstruction. In addition, patients undergoing a liver biopsy are required to have an international normalized ratio <1.6 and platelet count >60 × 10^9^/L. For analysis of the histological end point, patients who can be evaluated must have adequate baseline biopsy specimens with a METAVIR necroinflammatory or fibrosis score of at least 1. Progression of hepatic fibrosis or necroinflammatory progression is defined as an increase of at least 1 point.

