## Methods/design

### Study design

This large, prospective, multicenter, centrally randomized, double-blind, placebo-controlled trial is being conducted in nine institutions between November 2013 and November 2018. The study meets the requirements of the Declaration of Helsinki, and has been approved by the ethics committees of each participating institution. All patients with CHB or HBV-related compensated cirrhosis are carefully screened by a multidisciplinary team to select suitable candidates for this clinical trial, according to the inclusion and exclusion criteria of the present RCT and the patients’ willingness to participate in the study. For the study, 1,000 patients are being randomly assigned in a 1:1 ratio to one of two groups: a treatment group (0.5 mg ETV once daily; 2 g RGT three times daily) or a control group [0.5 mg ETV once daily; 2 g RGT dummy agent (similar in taste, shape and color to RGT; main ingredients include pearl barley and grilled germinate barley) three times daily]. During the double-blind phase, unblinding will take place as soon as sufficient evidence indicates: (1) that the effect of RGT plus ETV blocking and reversing hepatic fibrosis (measured by METAVIR system) is statistically superior to that with ETV alone, (2) that RGT plus ETV does not provide a significant advantage over ETV alone by the second liver biopsy at week 72 of double-blind treatment or (3) safety concerns. Patients who reach an end point are offered open-label RGT plus ETV or ETV alone for 1 year, and patients who have blockade and reversal of hepatic fibrosis are followed up after treatment and have the option to receive RGT plus ETV as an open-label treatment in the event of hepatic fibrosis or necroinflammatory progression. However, patients with stable or reversed disease will continue to receive antiviral therapy with ETV alone, but those with disease progression will receive open-label RGT plus ETV as in the control group. The study will be terminated as soon as sufficient evidence indicates that the outcome of patients with CHB or HBV-related compensated cirrhosis by RGT plus ETV blockade and reversal of hepatic fibrosis is statistically superior to that with ETV alone or does not provide a significant advantage over ETV. If the trial is terminated according to the predefined criteria, patients will be offered open-label treatment for 1 year. Liver biopsies are performed at three defined time points: before the start of randomization (pretreatment), at week 72 of the double-blind treatment, and at month 24 of the open-label treatment in the follow-up study. After 24 weeks of treatment, any patients with a reduction in HBV DNA level from baseline <1 log IU or 2 log copies/mL will be treated with a combination of ETV and adefovir dipivoxil (10 mg once daily) against HBV. The flow chart of the study is shown in Figure 1.

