### Participants and eligibility

Inclusion criteria are as follows: (1) men or women aged 18 to 65 years; (2) persistent serum HBsAg for ≥6 months; (3) serum HBV DNA ≥2000 IU/mL or ≥10,000 copies/mL; (4) baseline liver fibrosis (liver biopsy) stage F ≥2 (METAVIR system); (5) TCM syndrome type: blood stasis, or blood deficiency with toxic heat retention and (6) no antiviral or antifibrotic therapy for 6 months. Patients are excluded if they have any of the following at enrollment: (1) history of concurrent malignancy, including HCC; (2) baseline liver fibrosis (liver biopsy) stage F <2 (METAVIR system); (3) immunosuppression (organ transplantation or immunosuppressant use); (4) severe alcoholism; (5) serious uncontrollable heart, kidney, lung, endocrine, blood, metabolic or gastrointestinal primary disease, or mental illness; (6) pregnancy or lactation; (7) allergic constitution or allergic to TCM use; (8) no prescribed medication, poor compliance, incomplete data affecting the efficacy and safety of those judgments; (9) unsuitable for this trial according to the researchers or (10) co-infection with hepatitis C or D virus or HIV.

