### Statistical methods

The randomized subjects who have taken at least one dose of study drug and are evaluated for at least once curative effect after taking medication, constitute the full analysis set and safety analysis set. Those who complete all the visits comprise the per-protocol set. The statistical analysis will be performed using SAS 9.1 software (SAS Institute, Cary, NC, USA). The overall loss rate due to adverse events of each group will be calculated. When subjects enter the trial, they are assessed for demographic data, baseline condition and other essential information and are compared between groups. Cumulative incidence of HCC and overall survival rate will be determined by Kaplan–Meier analysis, and the log-rank test will be used for treatment comparisons. Changes from baseline in liver histology (METAVIR score) as well as in liver and spleen imaging (type B ultrasound) between the two groups will be compared by the Cochran–Mantel–Haenszel test. Changes from baseline in serum markers for liver fibrosis and liver function, transient electrograph (FibroScan) and TCM syndrome between the two groups will be compared by a covariance or non-parametric test. The statistical significance is defined as a two-sided *P* <0.05.

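### Baseline F4 patients cannot rise a METAVIR fibrosis stage but stay in the histologically evaluable set, so any fibrosis-progression rate is diluted, equally in both arms

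*Protocol article*

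**What the plan says.** All of the following is in the protocol article, under Methods/design.

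- **Who is enrolled.** Study design: "All patients with CHB or HBV-related compensated cirrhosis are carefully screened by a multidisciplinary team". Participants and eligibility requires "baseline liver fibrosis (liver biopsy) stage F ≥2 (METAVIR system") and excludes only "baseline liver fibrosis (liver biopsy) stage F <2 (METAVIR system"). F2, F3 and F4 are therefore all eligible.
- **The scale.** Study design, text after Figure 1, lists the fibrosis stages as "no fibrosis (F0), mild fibrosis (F1), moderate fibrosis (F2), severe fibrosis (F3) and cirrhosis (F4"). Nothing lies above F4. Activity is graded separately, from A0 to A3.
- **The progression rule.** In the same section, disease progression is either "histological progression reflected by an increase in METAVIR score of at least 1 point" or the occurrence of decompensated cirrhosis. That sentence does not say whether the METAVIR score means stage, activity grade or either. The paragraph on biopsy contraindications then sets the same one-point threshold for fibrosis progression and for necroinflammatory progression.
- **Who is evaluable.** The contraindications paragraph asks for an adequate baseline biopsy with a fibrosis or necroinflammatory score of 1 or more. It gives no maximum and no separate rule for baseline F4.
- **The test.** Statistical methods says that changes from baseline in liver histology "between the two groups will be compared by the Cochran–Mantel–Haenszel test". No strata are named.

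**The concern.** A patient who starts at F4 has no stage to rise to. If fibrosis progression is reported over all histologically evaluable patients, part of the denominator was never at risk, and the size of that part depends on how many patients with cirrhosis each centre happens to enrol. The rate then cannot be compared with other populations. It also understates how often fibrosis worsens in the patients in whom worsening can be seen.

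Within the composite, the histological limb also means different things by baseline stage. In F2-F3 it can record worsening fibrosis. In F4 it can record at most a rise in activity, and only if activity is part of the score. What is at stake is the interpretation of a component of a secondary end point, plus a little precision. The primary end points, HCC and liver-related death, are untouched.

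**Working it through.** **Logical check.** For baseline F4 the largest possible stage change is 4 − 4 = 0, and the rule needs at least 1. The probability of fibrosis progression is therefore 0 in both arms. With F4 share *f* and progression rate *p* in F2-F3, the rate over all evaluable patients is

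(1 − *f*) × *p* + *f* × 0 = (1 − *f*) × *p*.

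The rate in each arm and the difference between arms both shrink by the factor (1 − *f*). The ratio between arms does not change.

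**Inputs for the size.** The article's sample-size figures concern fibrosis reversal. It states no figure for progression, so there is none to reproduce.

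- From Sample size and Randomization: 500 per arm and up to 45% accepted for a second biopsy, so at most 500 × 0.45 = 225 biopsied per arm.
- From Statistical methods: two-sided 0.05.
- Assumed, not in the article: F2-F3 progression of 20% (control) v 10% (treatment), and an F4 share of 20%, 30% or 50%.

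**Formula.** Two proportions, *n* per arm, pooled variance under the null:

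power = Φ{[|p1 − p2| × √n − 1.96 × √(2 × p̄ × (1 − p̄))] / √[p1(1 − p1) + p2(1 − p2)]}

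Worked example at 20% F4:

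- *F4 kept in.* Rates 0.16 v 0.08, n = 225, p̄ = 0.12: (0.08 × 15 − 1.96 × √0.2112) / √0.208 = (1.200 − 0.901) / 0.456 = 0.656, so power is 0.744.
- *F2-F3 only.* Rates 0.20 v 0.10, n = 225 × 0.8 = 180, p̄ = 0.15: (0.10 × 13.416 − 1.96 × √0.255) / √0.25 = (1.342 − 0.990) / 0.500 = 0.704, so power is 0.759.

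| F4 share | Rates, F4 kept in | Power, F4 kept in | n per arm, F2-F3 only | Power, F2-F3 only | Gain (points) |
|---|---|---|---|---|---|
| 0% | 20% v 10% | 0.846 | 225 | 0.846 | 0 |
| 20% | 16% v 8% | 0.744 | 180 | 0.759 | 1.5 |
| 30% | 14% v 7% | 0.679 | 157.5 | 0.702 | 2.3 |
| 50% | 10% v 5% | 0.521 | 112.5 | 0.556 | 3.5 |

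The ratio of rates is 2 in every row. With assumed F2-F3 rates of 15% v 8% instead, power at the same three F4 shares goes from 0.538 to 0.549, 0.480 to 0.495 and 0.357 to 0.376. That is a gain of 1.1, 1.5 and 1.9 points.

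**Chance imbalance.** At 30% F4, one standard deviation of the difference in F4 share between arms is √(2 × 0.3 × 0.7 / 225) = 0.043. Multiplied by a 20% progression rate, it moves the result by about 0.9 percentage points.

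**The case against.** The strongest reply is that fibrosis-stage progression is not a named end point. The named one is a composite, and decompensation is the event one would want to count in patients who already have cirrhosis. If the METAVIR score includes activity, an F4 patient below A3 has a histological route as well. This stands. A reader might infer that F4 patients are scored as non-progressors on the whole secondary end point. The text does not support that, and the point is limited to the fibrosis component.

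A second reply is that the ceiling applies to both arms alike. This also stands: under randomisation it dilutes and does not bias, the ratio of rates is unchanged, and chance imbalance in F4 is small and part of ordinary random error.

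A third concerns power. Reading down the table, one could say that the rule cuts power from 85% to 52%. That comparison is with a trial that enrols no F4 patients, so most of the fall reflects fewer patients at risk and would remain after any redefinition. Only the gain column belongs to the rule.

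A fourth concerns the test. The Cochran–Mantel–Haenszel test is stated for change from baseline, in which F4 patients can improve, and naming strata is a detail that a condensed article may leave to the analysis plan. The absence of strata is therefore not counted as an error here. Stratification is offered as part of the remedy.

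What no reply removes is the denominator. The article itself sets the scale, the threshold and the evaluability rule, and together they keep F4 patients in any fibrosis-progression rate.

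**Conclusion.** The point holds as a minor, inexpensive improvement. It is certain from the text that baseline F4 patients count as histologically evaluable and cannot show fibrosis progression, so the rate is multiplied by one minus the F4 share in each arm. The size in this trial cannot be computed, because the article gives neither that share nor a progression rate. Under the main assumptions (20% v 10% in F2-F3, 225 biopsied per arm, 20% to 50% F4), separating out F4 gains about 1.5 to 3.5 points of power. Under 15% v 8% the gain is 1.1 to 1.9 points. The main benefit is a rate that means the same thing for every patient in its denominator.

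The documents do not support a claim of bias, of a composite closed to F4 patients, or of a large power loss caused by the rule. Nor do they call for redefining the composite in F4 as decompensation only. That would discard any activity worsening in those patients, which is a trade-off and not a correction.

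**What to change.** 1. Keep the composite disease-progression end point in all patients, and state whether the METAVIR score in its histological limb means stage, activity grade or either.
2. Report the fibrosis-progression component, a rise of at least one F stage, in patients with baseline F2-F3 only.
3. Report activity progression as a separate component.
4. Stratify the Cochran–Mantel–Haenszel comparison by baseline fibrosis stage. For a yes/no fibrosis-progression outcome, an F4 stratum has no events and so adds nothing to the test statistic. For the change score, F4 patients still contribute through improvement.

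Baseline stage is measured in every patient as an entry criterion, so no new data are needed. The cost is a change of wording, to be made before unblinding, and a smaller denominator for the fibrosis component: 180 to 112.5 per arm instead of 225 under the assumed F4 shares. The change concerns analysis and reporting only, not how patients are managed when they progress.

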### Follow-up

At baseline, all patients are screened to confirm the absence of HCC using abdominal ultrasonography and laboratory analyses, including AFP level. During the follow-up, all patients are seen at 3- to 6-month intervals. Periodic surveillance is also performed with abdominal ultrasonography and laboratory analyses, including AFP level, every 3 or 6 months to screen for HCC and other complications related to portal hypertension. Patients also undergo endoscopy every 1 or 2 years for screening and follow-up of gastroesophageal varices. HBV DNA, hepatitis B surface antigen (HBsAg), anti-HBs, hepatitis B e antigen, anti-HBe, and routine hematological and biochemical tests are performed. Adverse events that have occurred since the previous visit are recorded, and toxicity is graded according to predefined criteria.

### Participants and eligibility

Inclusion criteria are as follows: (1) men or women aged 18 to 65 years; (2) persistent serum HBsAg for ≥6 months; (3) serum HBV DNA ≥2000 IU/mL or ≥10,000 copies/mL; (4) baseline liver fibrosis (liver biopsy) stage F ≥2 (METAVIR system); (5) TCM syndrome type: blood stasis, or blood deficiency with toxic heat retention and (6) no antiviral or antifibrotic therapy for 6 months. Patients are excluded if they have any of the following at enrollment: (1) history of concurrent malignancy, including HCC; (2) baseline liver fibrosis (liver biopsy) stage F <2 (METAVIR system); (3) immunosuppression (organ transplantation or immunosuppressant use); (4) severe alcoholism; (5) serious uncontrollable heart, kidney, lung, endocrine, blood, metabolic or gastrointestinal primary disease, or mental illness; (6) pregnancy or lactation; (7) allergic constitution or allergic to TCM use; (8) no prescribed medication, poor compliance, incomplete data affecting the efficacy and safety of those judgments; (9) unsuitable for this trial according to the researchers or (10) co-infection with hepatitis C or D virus or HIV.

### Recruitment

Nine first-class hospitals across the Eastern, Western, Southern, Northern and Central areas of China are involved in this clinical trial. Participants are recruited via posters at each participating center.

### Randomization

This study has two arms. Once enrolled, participants who meet the inclusion criteria are informed about the study and treatment plan. Written informed consent is obtained when the patient accepts this plan and is willing to participate. A consecutively numbered envelope is unsealed by a research assistant. The sealed numbers are generated by a computerized random number generator with SAS software by Boao Tong Medical Technology Co Ltd (Beijing, China) and are concealed and disseminated using opaque envelopes. Based on this number, the patient is randomly assigned in a 1:1 ratio to the treatment group (ETV + RGT, *n* = 500) or control group (ETV + RGT-dummy agent, *n* = 500).

### Sample size

We assumed that the rate of hepatic fibrosis reversal would be 39% in the ETV-treated patients at the end of 2 years [26, 27], and 61% in the RGT-treated patients. Using PASS 2002 statistical software (NCSS, Kaysville, UT, USA), we calculated that we need two groups of 186 cases, and each group needs to enroll 223 cases if there is a drop-out rate of 15%, that is, a total of 446 cases. Currently, up to 45% of all enrolled patients will be accepted for a second liver biopsy. A total of 500 cases is required in each group to achieve a power of 0.80 and a significance level of 0.05 in assessing the difference between the two groups.

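### The only power figure, 0.80, comes from a fibrosis-reversal calculation that it does not fit, and no power calculation supports the primary comparison of HCC and liver-related death

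*Protocol article*

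**What the plan says.** All quotes are from the protocol article.

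- **Primary end points (Study design):** "The primary end points in this study are the occurrence of HCC or liver-related mortality".
- **Secondary end points (Study design):** "Secondary end points are disease progression and overall survival rate". The histological part of disease progression is a METAVIR increase of at least 1 point, which is worsening.
- **Sample size, assumption:** "We assumed that the rate of hepatic fibrosis reversal would be 39% in the ETV-treated patients at the end of 2 years", "and 61% in the RGT-treated patients".
- **Sample size, steps:** "we calculated that we need two groups of 186 cases"; then "each group needs to enroll 223 cases if there is a drop-out rate of 15%, that is, a total of 446 cases"; then "up to 45% of all enrolled patients will be accepted for a second liver biopsy".
- **Sample size, conclusion:** "A total of 500 cases is required in each group to achieve a power of 0.80 and a significance level of 0.05". The sentence goes on to speak only of a difference between the groups and does not say in which outcome.
- **Statistical methods:** a log-rank test for HCC incidence and overall survival, a Cochran–Mantel–Haenszel test for change in METAVIR score, and two-sided significance at 0.05.

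**The concern.** The declared question is whether adding RGT to entecavir reduces HCC and liver-related death. The size of the trial was set on a different outcome, and the section then closes with a power figure attached to no outcome. A reader who knows the primary end points may take 0.80 to be the power for them.

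This has consequences because the Study design and Data and safety monitoring board sections allow termination when the combination shows no significant advantage over entecavir alone. If non-significance can end the trial, the power behind the comparison decides how that result should be read. A null HCC result credited with 80% power would look like evidence of no effect, when the trial might have been able to detect only a large one.

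**Working it through.** **1. Where 500 per group comes from.** 186 is raised to 223 for drop-out, and 223/0.45 = 496, or about 500. Every input is a fibrosis-reversal or biopsy-uptake figure. (The 15% step does not give 223 exactly: 186/0.85 = 219, while 186 × 1.20 = 223. The difference is small.)

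**2. Does 186 correspond to power 0.80?** Inputs from the article: p1 = 0.39, p2 = 0.61, two-sided 0.05, 1:1 allocation. The mean proportion is 0.50.

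n per group = [1.960·√(2·0.5·0.5) + 0.8416·√(0.39·0.61 + 0.61·0.39)]² / 0.22²
= (1.3859 + 0.5805)² / 0.0484 = 79.9, so 80 (89 with continuity correction).

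The stated 186 is not reproduced. The power for a given n is Φ[(0.22·√n − 1.3859)/0.6898]:

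| Evaluable per group | Origin | Power for reversal |
|---|---|---|
| 80 | needed for 0.80 | 0.80 |
| 186 | stated | 0.990 |
| 191 | 225 less a further 15% | about 0.99 |
| 225 | 45% of 500 | 0.997 |

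Of the power levels tried (0.80 to 0.99, two-sided 0.05, no continuity correction), only 0.99 comes close to 186; it gives 185 per group.

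**3. Timing.** The 39% is assumed at the end of 2 years, but the Study design section places the second biopsy at week 72 (72/52 = 1.4 years).

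**4. Is reversal covered by the secondary end point?** No. Disease progression counts worsening or decompensation. A patient with stable histology has neither reversal nor progression, so one is not the complement of the other.

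**5. The primary comparison.** The article gives no control rate, hazard ratio (HR) or event count, so no single figure can be derived. Events needed for 80% power by Schoenfeld's formula, 4(1.960 + 0.8416)²/(ln HR)², are 66 for HR 0.5, 121 for HR 0.6 and 247 for HR 0.7.

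The following is an illustration only. The assumptions are mine: exponential event times, control rate r of 1% to 3% per year, mean follow-up 4 years, no drop-out.

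Events d = 500(1 − e^(−4r)) + 500(1 − e^(−4r·HR)); power = Φ(|ln HR|·√d/2 − 1.96).

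| r per year | d at HR 0.5 | Power, HR 0.5 | d at HR 0.7 | Power, HR 0.7 | HR detectable at 80% |
|---|---|---|---|---|---|
| 1% | 30 | 0.47 | 33 | 0.18 | 0.34 |
| 2% | 58 | 0.75 | 66 | 0.30 | 0.48 |
| 3% | 86 | 0.89 | 97 | 0.42 | 0.55 |

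If 15% of events are lost (d × 0.85), power for HR 0.7 falls to about 0.16 at 1% and 0.37 at 3%.

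**6. The same question by cumulative incidence.** With 500 per group and no drop-out, 80% power requires a control incidence over follow-up of about 8.7% for HR 0.5, 14.9% for HR 0.6 and 28.5% for HR 0.7.

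**The case against.** **Fibrosis has a visible role in the plan.** METAVIR blockade and reversal is an unblinding criterion, the week 72 biopsy is a decision point, the article refers to a histological end point, and change in METAVIR score has an assigned test. Sizing on it therefore has a purpose. This stands: reversal is not absent from the plan. But it is still not among the listed primary or secondary end points, and its role gives no information about power for the log-rank comparison of HCC.

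**A reader might infer that the HCC question has no power, or that the trial is underpowered.** The documents do not support that. Power is uncalculated, and it could be adequate if the effect is large and events are frequent: 0.89 at 3% per year with HR 0.5, and 0.99 at a control incidence of 20% with HR 0.5.

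**A reader might also infer that 0.80 is simply the power for reversal, mislabelled.** The article's own inputs contradict that (step 2).

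**The illustration rests on outside assumptions.** This is correct. It also ignores possible unblinding around week 72 and open-label RGT for patients who progress, either of which would affect the contrast. It shows sensitivity and is not an estimate for this trial.

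**The section opens by naming fibrosis reversal, so a careful reader can see what was powered.** That is true of the assumption. It is less true of the closing sentence, which names no outcome. How a null result would be read is a prediction, and the two termination provisions are what make it matter.

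**An unseen analysis plan might hold an HCC power figure.** It might, but the mismatch is between statements printed in the article, which already fixes the basis for 1,000 patients.

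**Conclusion.** The concern holds in this form. The only power statement is derived wholly from fibrosis reversal, 39% against 61%, an outcome that is analysed and used for unblinding but not listed as primary or secondary. No power calculation supports the comparison of HCC and liver-related death, so 0.80 must not stand as the trial's power for it.

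The figure is also wrong for reversal, where the planned numbers give about 0.99 or more if the 39% and 61% hold. That part rests only on the article's own inputs and the standard two-proportion formula.

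How far power for the primary comparison falls short of 0.80, if it does, cannot be determined from the article. The detectable hazard ratios and powers shown depend on the assumed rates and follow-up.

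**What to change.** In the Sample size section:

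1. State that 500 per group was set on fibrosis reversal at the second biopsy. Re-derive the power for that outcome instead of attaching 0.80 to it, and reconcile the 2-year assumption with the week 72 biopsy.
2. Name fibrosis reversal as a secondary end point, as a dated change, since recruitment is ongoing.
3. For HCC and liver-related death, replace the implied 0.80 with the assumed control rate and its source, the number of events expected by November 2018 after allowing for the 15% drop-out, and the hazard ratio detectable with 80% power at 500 per group.

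Report the primary result as a hazard ratio with its confidence interval, and do not read non-significance as absence of effect.

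The cost is rewording and one recalculation, with no extra patients. The downside is that the stated power for the primary end point is likely to look less favourable. The change makes the trial's sensitivity visible but does not increase it.

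### The stated effect, alpha and power need 80 to 89 evaluable biopsies per group, so neither the 186 nor the 500 per group at power 0.80 follows from them

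*Protocol article*

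**What the plan says.** All the figures are in the Sample size section of the protocol article, apart from the sidedness of the test and the biopsy schedule.

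- **Effect:** "the rate of hepatic fibrosis reversal would be 39% in the ETV-treated patients at the end of 2 years", "and 61% in the RGT-treated patients".
- **First result and drop-out:** "we need two groups of 186 cases, and each group needs to enroll 223 cases if there is a drop-out rate of 15" per cent, which the text totals as 446.
- **Biopsy uptake:** "Currently, up to 45% of all enrolled patients will be accepted for a second liver biopsy".
- **Final size:** "A total of 500 cases is required in each group to achieve a power of 0.80 and a significance level of 0.05".
- **Sidedness** (Statistical methods): "The statistical significance is defined as a two-sided" P below 0.05.
- **Biopsy timing** (Study design, end-point text): one biopsy before randomization, then "at week 72 of the double-blind treatment and at month 24 of the open-label treatment during follow-up".

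No power other than 0.80 appears anywhere in the article.

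**The concern.** A difference of 22 percentage points around 50% is large, and a two-group comparison of proportions rarely needs 186 per group to detect it with 80% power. If the figures do not follow from the inputs, the article states a design property that the trial does not have.

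This matters for how the histology result is read. Under Study design, the evidence on fibrosis up to the week-72 biopsy can lead to unblinding, either for superiority or for lack of a significant advantage. The Data and Safety Monitoring Board may recommend termination on similar grounds. What a non-significant result rules out depends on the true power. A board told that it has 80% power for 22 points would misjudge that.

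**Working it through.** **Inputs.** p1 = 0.39, p2 = 0.61, power 0.80 and alpha 0.05 (Sample size); two-sided test (Statistical methods); 1:1 allocation (Randomization). The mean proportion is 0.50 and the difference is 0.22.

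**1. Trying to reproduce 186.** Pooled two-proportion formula, per group:

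n = [z(0.975)·√(2·0.50·0.50) + z(0.80)·√(0.39·0.61 + 0.61·0.39)]² / 0.22²

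= [1.960 × 0.7071 + 0.8416 × 0.6898]² / 0.0484 = (1.3859 + 0.5805)² / 0.0484 = 79.9, so **80**.

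Continuity correction: (79.9/4)·[1 + √(1 + 4/(79.9 × 0.22))]² = 88.8, so **89**.

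Other settings, per group:

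| Setting | n | n with continuity correction |
|---|---|---|
| One-sided 0.05, power 0.80 | 63 | 72 |
| Two-sided 0.05, power 0.80, unpooled variance | 78 | – |
| Two-sided 0.05, power 0.80, arcsine | 80 | – |
| Two-sided 0.05, power 0.80, Fisher exact | about 86–93 | – |
| Two-sided 0.01, power 0.80 | 120 | 129 |
| Two-sided 0.05, power 0.90 | 107 | 116 |
| Two-sided 0.05, power 0.95 | 132 | 141 |
| Two-sided 0.05, power 0.99 | 185 | 194 |

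No 80%-power variant gives 186 per group. The stated figure is 186/89 = 2.1 to 186/80 = 2.3 times what the inputs need.

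**2. Power at the stated sizes.** Power = Φ[(0.22·√N − 1.3859) / 0.6898].

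- N = 186: Φ(2.34) = **0.990**.
- N = 225, that is 500 × 0.45, no other loss: Φ(2.77) = **0.997**.
- N = 191, that is 500 × 0.85 × 0.45 = 191.25: Φ(2.40) = **0.992**.

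**3. What the planned 500 can detect.** The same formula, solved for the RGT rate at 80% power with 39% in the control group, gives 52.1% with 225 pairs and 53.2% with 191. These are differences of about 13 to 14 points.

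**4. Enrolment that the stated inputs imply.** Applying both the 15% and the 45%: 80/0.85/0.45 = 209.2, so 210 per group. With continuity correction, 89/0.85/0.45 = 232.7, so 233.

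**5. Drop-out step.** 186/(1 − 0.15) = 218.8, so 219. The stated 223 equals 186 × 1.20 = 223.2 and implies a loss of 1 − 186/223 = 16.6%. The gap is 4 patients per group, or 1.8%.

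**6. Where 500 may come from.** 223/0.45 = 495.6, close to 500. The article does not show this division, so it is an inference. If it is right, an upper limit on uptake was used as the expected value.

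**The case against.** - **The 0.80 is not written beside 186.** This stands. The article attaches 0.80 to the 500 per group, and 186 may come from a software run at a power that the condensed text omits. A reader might infer that the article claims 80% power for 186, but it does not say so. Nor can one say that 99% was intended: that value is back-fitted, and the exact result at 0.99 is 185. The mismatch remains all the same, because 0.80 fits neither 186 nor 500.
- **186 could be a total.** That would be 93 per group, where Fisher's exact test has power 0.815, so the reading is not far off. The text rules it out as written: it speaks of two groups of that size and doubles the inflated figure to reach 446.
- **The error is conservative.** This also stands. It overstates the number needed, so the fibrosis comparison is not underpowered. No analysis or allocation changes.
- **The trial might look oversized.** The 210 to 233 per group could be read that way. The document does not support it. The calculation concerns fibrosis reversal only, whereas the primary end points are HCC or liver-related death, and no calculation in the article sizes those.
- **219 against 223 is trivial.** Agreed. It is small and errs on the safe side.
- **The two-year rates come from cited sources not shown here.** True, so the effect of the timing difference on n cannot be quantified. The difference itself is visible in the text.

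**Conclusion.** The point holds. On the only effect, alpha and power stated, 80 to 89 evaluable pairs per group are needed, against 186. The 500 per group carries power of 0.992 to 0.997 for 39% against 61%, not 0.80. The paragraph is therefore wrong as written, by a factor of about 2.1 to 2.3 in the evaluable number.

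This rests on a two-sided 0.05 test of two independent proportions with 1:1 allocation. The 225 pairs assume that the full 45% is reached with no other loss. The 191 assumes that the 15% drop-out applies as well. If uptake falls below 45%, both figures are too high.

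The error does not weaken the fibrosis comparison. It does not show that fewer patients should be enrolled, and it says nothing about power for HCC or liver-related death. The drop-out figure and the timing of the assumed rates are minor.

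**What to change.** Keep 500 per group and rewrite the Sample size paragraph in one of two ways:

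1. State the power or effect size from which 186 was actually derived, and make the final sentence on 500 per group agree with it.
2. Or state that 80 evaluable biopsy pairs per group (89 with continuity correction) give power 0.80 for 39% against 61%. Add that the planned 500 per group gives about 191 to 225 pairs, with power of about 0.99 for 61%, or 0.80 for about 52% to 53%. Mark 225 as an upper limit.

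In either case, say that this power refers to fibrosis reversal at biopsy only and not to the primary end points of HCC and liver-related death.

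Two smaller corrections belong in the same edit. Replace 223 (446 in total) with 219 (438 in total), or state the loss rate actually used. Reconcile the assumed two-year reversal rates with the biopsy at week 72 of double-blind treatment.

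The cost is one rewritten paragraph, with no change to enrolment, allocation or analysis.
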